## Abstract

**Background:**

Hip and knee osteoarthritis is a common cause of pain and disability, which can be improved by exercise interventions. However, regular exercise is uncommon in this group because the low physical activity level in the general population is probably reduced even further by pain related fear of movement. The best method of encouraging increased activity in this patient group is not known. A booklet has been developed for patients with hip or knee osteoarthritis. It focuses on changing disadvantageous beliefs and encouraging increased physical activity.

**Methods/Design:**

This paper describes the design of a Phase II randomised controlled trial (RCT) to test the effectiveness of this new booklet for patients with hip and knee osteoarthritis in influencing illness and treatment beliefs, and to assess the feasibility of conducting a larger definitive RCT in terms of health status and exercise behaviour. A computerised search of four general medical practice patients' record databases will identify patients older than 50 years of age who have consulted with hip or knee pain in the previous twelve months. A random sample of 120 will be invited to participate in the RCT comparing the new booklet with a control booklet, and we expect 100 to return final questionnaires. This trial will assess the feasibility of recruitment and randomisation, the suitability of the control intervention and outcome measurement tools, and will provide an estimate of effect size. Outcomes will include beliefs about hip and knee pain, beliefs about exercise, fear avoidance, level of physical activity, health status and health service costs. They will be measured at baseline, one month and three months.

**Discussion:**

We discuss the merits of testing effectiveness in a phase II trial, in terms of intermediate outcome measures, whilst testing the processes for a larger definitive trial. We also discuss the advantages and disadvantages of testing the psychometric properties of the primary outcome measures concurrently with the trial.

**Trial registration:**

Current Controlled Trials ISRCTN24554946

## Background

Systematic reviews have highlighted the effectiveness of exercise in reducing pain and disability in hip and knee osteoarthritis [1-4] and recent guidelines have emphasised the central role of exercise in the management of osteoarthritis [5,6]. Both aerobic walking and muscle strengthening exercise have been shown to be effective; however the optimal type, dose and setting for such physical activity is uncertain [3,7]. Despite these benefits, long-term adherence to exercise regimes is disappointing, and if exercise is not maintained its beneficial effects decline over time and finally disappear [8]. The level of physical activity in older adults in the United Kingdom is low [9-12], and reduced further by pain related fear of movement in those with osteoarthritis [13,14]. Indeed, there is a culturally conditioned response to pain that encourages rest, which is inappropriate for most with this problem. How can osteoarthritis patients be encouraged to increase their physical activity? In the similar field of low back pain an evidence-based patient advice booklet ('The Back Book' [15]) designed to encourage activity was found to be effective in changing patients' beliefs and behaviours. The effectiveness of this 'Back Book' was demonstrated in three randomised controlled trials (RCTs) [16-18], one of which involved older people.

### Developing 'The Hip and Knee Book'

We have developed a similar booklet encouraging increased activity in patients with hip or knee osteoarthritis. The theoretical framework underpinning this new booklet is Leventhal's theory of self regulation, which states that our coping response to illness is governed by our beliefs about the nature of the illness: how well we understand the symptoms (its identity), its chronicity, its controllability, its cause, and the seriousness of its consequences [19]. Educational interventions should emphasise that control is possible and within individuals' capabilities. This model has been extended to include treatment beliefs, so that when considering an intervention patients weigh up the perceived benefit in health gain with the perceived cost in terms of pain, fear and expectation of exacerbating the condition [20]. In addition, social learning theory states that an individual's ability to perform an activity (self-efficacy) is crucial to behaviour change [21]. The evidence based messages for this booklet were obtained from a review of systematic reviews and evidence based management guidelines. These were then converted into patient centred messages and combined in the narrative of a draft booklet. This draft booklet was examined in four focus groups of patients with hip or knee osteoarthritis, which improved the phrasing and emphasis of the patient centred messages in the final booklet [22]. The development of this booklet has been described in more detail elsewhere [23]. This paper reports upon the design of a RCT to test the effectiveness of this new booklet for patients with hip and knee osteoarthritis in terms of influencing illness and treatment beliefs, and to assess the feasibility of conducting a larger definitive RCT to measure change in health status and exercise behaviour [24].

## Methods/Design

### Study design

This study has several overlapping aims. In order to test the effectiveness of the new 'Hip and Knee Book' for changing illness and treatment related beliefs a RCT design is employed using outcome measures designed to measure such beliefs. We also want to assess the feasibility of conducting a future definitive RCT and concurrent economic evaluation of the effectiveness and cost-effectiveness of this new booklet on health status and exercise behaviour, so we will use this RCT to pilot recruitment and retention of participants recruited from primary care with hip or knee osteoarthritis, measure changes in health status, levels of physical activity and public agency costs. The results will inform the sample size calculation for a future Phase III RCT. We have developed instruments measuring illness and treatment beliefs from outcome measures designed for different purposes, so we will use this RCT to concurrently test the validity and responsiveness of these adapted instruments.

### Recruitment

#### Practice and participant selection

Participants will be recruited from four general medical practices in Wrexham and Flintshire in North East Wales in the United Kingdom. Patients with hip and knee osteoarthritis will be identified by searching the practices' computerised patient record database for the relevant Read codes (Table 1). Anonymised unique patient identification numbers will be downloaded onto an Excel file and sent to the trial statistician, who will select a random sample of 400 patients with hip and knee osteoarthritis from all four practices. Additional patients will be placed on a reserve list. The Excel file containing the anonymised patient identification numbers will be returned to the practice management team, who will check that the patients fulfil the inclusion and exclusion criteria and that it is appropriate to invite them to participate in the study. Patients who are ineligible, or where an invitation to participate would be inappropriate, will be replaced by those on the reserve list. The practice management team will send eligible patients invitation letters to participate, signed by their general practitioner (GP) on the practices' headed note paper, including an information sheet about the trial and a consent form. We will invite the initial 400 sample to participate, and those on the reserve list as necessary, until we have reached our target of 120 participants (Figure 1).

**Figure 1 F1:**
[figure not shown]
**Participant flow diagram**.

**Table 1 T1:** Read codes for eligible patients (>50 years old)

**Included Read codes**	
N05 (and below)	osteoarthritis

14G2	H/O osteoarthritis

N06z5	hip arthritis

N06z6	knee arthritis

N094K	arthralgia of hip

N094M	arthralgia of knee

1M10	knee pain

**Excluded Read codes**	

M160	psoriatic arthropathy

N04 (and below)	inflammatory polyarthropathy

7K2 (and below)	hip joint operations

7K3 (and below)	knee joint operations

#### Inclusion and exclusion criteria

Patients over 50 years old presenting in primary care with hip or knee osteoarthritis within the last 12 months will be included. Specific diagnostic criteria for osteoarthritis will not be used as these are inconsistently applied in primary care populations. Exclusion criteria will be inflammatory joint disease, fractures, arthroplasty referral, and prescription of potent opioid analgesia. Patients who have already participated in the focus groups used to develop the new booklet will be excluded from the trial.

#### Informed consent

Patients will be sent an information sheet about the trial along with their letter of invitation and a consent form. The contact details of the research assistant co-ordinating recruitment will be included, and participants will be encouraged to ask for more information if they require it. The information sheet, letter of invitation and consent form will emphasise that patients' clinical care will remain unaffected whether they accept or decline to participate.

#### Withdrawal & loss to follow-up

We anticipate that 100 out of the 120 (80%) participants recruited will return their final questionnaires. Participant withdrawal from the study will not affect their medical care, and this point will be emphasised in the patient information sheet.

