### Sample size

In order to detect a moderate to large effect size of 0.55 in change in illness and treatment beliefs, with 80% power and a significance level of 5%, a sample size of 100 will be needed. We anticipate that 30% of those invited will agree to participate, and 80% of those recruited will return their final questionnaires; so that 400 patients will need to be sent letters inviting them to participate, 120 will be recruited, and 100 will return final questionnaires.

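### 80% retention of 120 recruited gives 96 completers, not 100, so the sample-size chain ends 4 short of its stated requirement (minor)

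*Protocol article*

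**What the plan says.** The Sample size section of the protocol article sets the requirement for an effect size of 0.55: "with 80% power and a significance level of 5%, a sample size of 100 will be needed". It then states two planning rates. For consent it says "We anticipate that 30% of those invited will agree to participate", and for retention "80% of those recruited will return their final questionnaires". From these it concludes that "400 patients will need to be sent letters inviting them to participate, 120 will be recruited, and 100 will return final questionnaires".

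The section on withdrawal and loss to follow-up puts the count and the percentage together: "We anticipate that 100 out of the 120 (80%) participants recruited will return their final questionnaires".

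The section on practice and participant selection has 400 patients drawn at random and invited, with a reserve list used as necessary "until we have reached our target of 120 participants".

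The abstract describes the first step differently: "A random sample of 120 will be invited to participate in the RCT comparing the new booklet with a control booklet". It also expects 100 final questionnaires, but gives no retention percentage.

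**The concern.** The Sample size section presents its counts as following from its rates, so a reader can check each link. The consent link holds and the retention link does not. The 80% stands in two sections, and in one of them it is an input to the calculation, so it cannot be set aside as a single misprint. Nothing else in the recruitment plan closes the gap, because the reserve list serves only to reach 120 recruited and does not replace losses after recruitment.

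At stake is whether the planned recruitment delivers the completer number on which the power statement rests. Estimating recruitment and retention is also one of the trial's aims, so the planning rates should at least be coherent.

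**Working it through.** **Inputs.** From the Sample size section: 400 invited, 30% consent, 120 recruited, 80% retention, 100 completers needed, effect size 0.55, power 80%, significance level 5%. The article does not state whether the test is two-sided or the allocation equal; both are assumed here.

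**The chain.**

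- Invited to recruited: 400 × 0.30 = 120. This agrees with the plan.
- Recruited to completers: 120 × 0.80 = 96. The plan says 100, so the shortfall is 100 − 96 = 4.
- Retention implied by the counts: 100 / 120 = 83.3%. The plan says 80%.
- Recruitment that 80% retention would require for 100 completers: 100 / 0.80 = 125, and 125 / 0.30 = 416.7, so 417 invited. These figures show the size of the mismatch and are not a proposal to enlarge the trial.

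**The plan's own 100.** For two means, n per arm = 2 × ((1.960 + 0.842) / 0.55)² = 51.9, which rounds up to 52 per arm or 104 in total (normal approximation). By the t-test it is 53 per arm, or 106. The stated 100 is therefore already slightly below what an unadjusted two-sided comparison needs for 80% power.

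**Power.** The noncentrality is 0.55 × √(n/2), with n per arm. For n = 48 it is 0.55 × √24 = 2.694, and for n = 50 it is 0.55 × √25 = 2.750. Under the normal approximation, power is Φ(noncentrality − 1.960); the t-test column uses the noncentral t distribution.

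| Completers | Per arm | Power, t-test | Power, normal | Effect detectable at 80% power (t-test) |
|---|---|---|---|---|
| 96 | 48 | 76.0% | 76.9% | 0.578 |
| 100 | 50 | 77.7% | 78.5% | 0.566 |

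The retention slip costs 77.7 − 76.0 = 1.7 points by the t-test, or 78.5 − 76.9 = 1.6 from the rounded normal figures (1.7 before rounding).

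**Abstract.** If only 120 were invited at 30% consent, 120 × 0.30 = 36 would be recruited. That contradicts both the 120 recruited in the Methods and the 100 completers in the abstract itself.

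**The case against.** **The 80% may be a loose label for 83.3%.** The count of 100 completers appears in the abstract and in both sections. If the count was meant and the percentage was rounded carelessly, recruiting 120 does deliver 100 and only the percentage is wrong. The text does not settle which was meant. This stands as a reason to offer two corrections, but on either reading one printed figure is wrong.

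**A reader might infer that the slip takes power from 80% to 76%.** It does not. By the same t-test, the full 100 completers give 77.7%. The rest of the distance to 80% comes from the 100 itself and has nothing to do with retention.

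**The unadjusted t-test is not the planned analysis.** The Main analysis section specifies baseline-adjusted repeated measures analysis of covariance by intention to treat, with imputation possible, and the effect size is expressed in terms of change. No correlation between baseline and follow-up is given. Assume a correlation r, equal variances and a single follow-up, with 0.55 standardised on the change score. The effect relative to the adjusted residual is then 0.55 × √(2 / (1 + r)). With 96 completers, power by the t-test is about 87% at r = 0.5, 82% at r = 0.7, 80% at r = 0.81 and 78% at r = 0.9. If 0.55 is standardised on the raw score instead, power is about 80% once r is about 0.3, and higher above that. This stands: 76% cannot be called the trial's power without qualification. Also, one-month data and imputation mean that the analysed set need not equal the three-month returners.

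**A reader might infer that retention between 80% and 83.3% would both meet and miss the plan.** The section on feasibility of the phase III trial sets no retention threshold. It lists the numbers to be reported, and later planning can use the observed rate. The documents do not support that harm.

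**The abstract is a separate matter.** It gives no retention rate, so it is not another version of the same error. The Methods agree on 400 invited and 120 recruited, and nobody following them would invite only 120.

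**Conclusion.** The error is certain and its consequence is minor. The two sections equate 100 of 120 with 80%, but 80% gives 96 and 100 of 120 is 83.3%. At the stated rate, the plan ends 4 below the completer number that it calls necessary.

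The cost is about 1.7 points of power, and the detectable effect moves from 0.566 to 0.578. These figures assume an unadjusted, two-sided comparison with equal arms. Under the planned adjusted analysis, power could be above or below 80%, depending on a correlation that the article does not state.

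Nothing in the design, conduct or choice of analysis changes. The abstract's wording on invitations is a further small inconsistency.

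**What to change.** Put one consistent chain in the Sample size section and in the section on withdrawal and loss to follow-up:

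- either 400 invited, 120 recruited, 80% retention and 96 completers;
- or 400 invited, 120 recruited, 83% retention (with a reason for expecting that rate) and 100 completers.

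Whichever is chosen, the power statement needs attention, because changing the percentage to 83% alone would leave an 80% power claim that 100 completers do not reproduce unadjusted. Either restate the unadjusted power (about 76–77% for 96, about 78% for 100), or state the baseline correlation, and the standard deviation behind the 0.55, under which the planned analysis of covariance reaches 80%.

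Separately, correct the abstract to say that 400 are invited and 120 recruited, and change its expected 100 questionnaires to 96 if the first chain is used.

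The cost is a few words and, if power is restated unadjusted, a slightly less favourable figure. No extra patients are needed.

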### Study intervention

Participants randomised to the intervention arm will be sent the new educational booklet by mail. This booklet 'The Hip and Knee Book: helping you cope with osteoarthritis' [22] describes the development of osteoarthritis as a dynamic process with the potential for some repair and discourages the more passive concept of 'wear and tear'. Physical activity is emphasised as being beneficial for arthritic joints, as well as for general physical health, and a variety of different types of exercise are promoted. Patients are also encouraged to lose weight if overweight, use simple analgesia and anti-inflammatory gels. Prescribed medication and additional methods to control pain are described. The role of different therapists is discussed as are specialist treatments including arthroplasty. The booklet emphasises that control over their condition is possible and within individuals' capabilities.

Participants randomised to the control arm will be sent a patient information booklet about osteoarthritis produced by the Arthritis Research Campaign (ARC) [25], which can be obtained from the ARC website, and is widely available in rheumatology out-patient clinics. This booklet discusses the mechanism of osteoarthritis, treatment options and self-management. Physical activity and exercise is mentioned, but not emphasised. In particular, it does not address the same exercise-related beliefs and behaviours as the intervention booklet. Clinical care of patients will not be affected or influenced in any other manner by participating in the study.

### Outcome measures

#### Primary outcome measures

The primary outcomes will be illness and treatment beliefs. Illness beliefs will be measured with the Hip and Knee Beliefs Questionnaire (HKBQ). This has been modified from the Backs Beliefs Questionnaire (BBQ) [26], and measures beliefs regarding the progressive nature of hip and knee osteoarthritis. Treatment beliefs will be measured with a modified Exercise Attitude Questionnaire-18 (EAQ-18) [27]. We have demonstrated the face validity of these questionnaires in semi-structured interviews using cognitive de-briefing [28]. We will collect data on the reliability, validity and responsiveness of these modified questionnaires concurrently with the trial analysis. Using a transition question we will place those who report no change into a reliability analysis and those who do report change into a responsiveness analysis.

### Trial procedures

#### Postal questionnaires

The questionnaires will follow best practice in their design to maximise response rate [36]. In particular, the questionnaire design will be: aesthetically pleasing using coloured ink; as short as possible; accompanied by a personalised letter using the university letter head; and sent by first class mail. Non-responders will be contacted by telephone, and sent a second copy of the questionnaire if required. Postal questionnaires will be sent at baseline, after one and three months, in Teleform^® ^format to allow scanning of responses into a computerised database. All data will be anonymised and coded so that data collection and statistical analysis will be blinded to treatment allocation.

#### Health economic data collection

Health economic costs will be measured from a National Health Service (NHS) perspective. Health service activity will be collected from responses to the CSRI incorporated into the final patient questionnaire. Patients will be asked about the type and frequency of contact with primary and secondary healthcare services over the three month period. Unit costs will be obtained from national sources [37] and local finance officers.

### Randomisation

Randomisation will balance the two groups by site of pain, age, gender and duration of symptoms. As all patients are consented prior to randomisation, this will use an optimal allocation approach proposed by Raab [38] and algorithms developed by Carter [39]. Patients will be recruited from each practice and then randomised as a block. Within the block all potential allocations to two groups will be calculated and their balance statistic calculated. The 1% with the nearest optimal balance will be passed to an independent statistician who will randomly select the allocation for use and randomly allocate groups. The balance calculations for subsequent blocks will incorporate the degree of balance for the chosen allocation to ensure close to optimal balance across groups.

### Sample size

In order to detect a moderate to large effect size of 0.55 in change in illness and treatment beliefs, with 80% power and a significance level of 5%, a sample size of 100 will be needed. We anticipate that 30% of those invited will agree to participate, and 80% of those recruited will return their final questionnaires; so that 400 patients will need to be sent letters inviting them to participate, 120 will be recruited, and 100 will return final questionnaires.

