#### Main analysis

Statistical analysis of the primary outcome measures HKBQ and EAQ-18 will be based on an intention to treat analysis using repeated measures analysis of covariance (ANCOVA). This method adjusts each patient's follow up score for his or her baseline measurements. Data transformations such as taking logarithms may be appropriate and any missing values can be imputed using regression techniques. The analysis will be expanded to include additional prognostic variables for exploratory analysis. There are assumptions underlying the ANCOVA model which include normality of residuals, equal variances, linearity, and independence. These assumptions will be tested, in particular the homogeneity of regression assumptions.

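### The stated total of 100 does not follow from the stated effect size, power and significance level; the conventional calculation gives 104 to 106 (minor)

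*Protocol article*

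**What the plan says.** The Sample size section sets the target difference: "In order to detect a moderate to large effect size of 0.55 in change in illness and treatment beliefs". It then gives the result: "with 80% power and a significance level of 5%, a sample size of 100 will be needed". It expects that "80% of those recruited will return their final questionnaires", and concludes that "120 will be recruited, and 100 will return final questionnaires".

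The section does not say whether the 5% is one-sided or two-sided, which test the figure is for, what the allocation ratio is, or which standard deviation the 0.55 is measured against. The Randomisation section confirms two groups: "Randomisation will balance the two groups by site of pain, age, gender and duration of symptoms". The Main analysis section plans repeated measures ANCOVA for both primary outcomes (HKBQ and EAQ-18) and says of it: "This method adjusts each patient's follow up score for his or her baseline measurements".

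**The concern.** An effect size, a power and a significance level fix the sample size of a two-group comparison once the test is chosen. On the usual choice the answer is a little above 100, so the printed figure errs in the favourable direction. The same section adds a second favourable slip: 80% of 120 is 96, not 100.

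This is the article's only power statement, and it covers both primary outcomes. One aim of the trial is to test whether the booklet changes beliefs, so a null result would be judged against the claimed 80%. A reader who tries to reproduce the figure cannot do so, and cannot tell whether an adjusted analysis was assumed.

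**Working it through.** **Inputs from the protocol article.** Effect size d = 0.55, power 80%, significance level 5%, total 100, 120 recruited, retention 80% (all Sample size); two groups (Randomisation); baseline-adjusted ANCOVA (Main analysis).

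**Assumptions.** Two-sided test and 1:1 allocation, so 50 per arm. Neither is stated.

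**1. Attempt to reproduce 100, unadjusted and two-sided.**

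- Normal formula: n per arm = 2 × (1.960 + 0.842)² / 0.55² = 51.9, so 52 per arm and 104 in total.
- Exact t: 52.87 per arm, so 53 per arm and 106 in total. Power is 79.3% at 52 per arm and 80.1% at 53.

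The stated 100 is not reproduced. The conventional figure is 4 to 6 people higher.

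**2. One-sided 5%.**

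- Normal formula: 2 × (1.645 + 0.842)² / 0.55² = 40.9, so 41 per arm and 82 in total.
- Exact t: 41.57 per arm, so 84 in total.

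On this reading 100 would be well above the requirement, so it does not explain the figure either.

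**3. What 100 and 96 completers deliver, unadjusted and two-sided.** Normal power is Φ(0.55 × √(n/2) − 1.960) with n per arm. The normal detectable effect is (1.960 + 0.842) × √(2/n).

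| Completers | Power, normal | Power, t | Effect detectable at 80%, normal | Same, t |
|---|---|---|---|---|
| 100 (50 per arm) | 78.5% | 77.7% | 0.560 | 0.566 |
| 96 (48 per arm) | 76.9% | 76.0% | 0.572 | 0.578 |

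The 96 is 120 × 0.80. To end with 100 at 80% retention, 100 / 0.80 = 125 would have to be recruited.

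**4. What baseline adjustment could add.** The article gives no correlation r between baseline and follow-up, so this is a range. It treats a single follow-up score.

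- *If 0.55 is scaled to the SD of the outcome*, ANCOVA multiplies the variance by 1 − r². Reaching 100 by the normal formula needs 1 − r² = 50 / 51.9 = 0.964, so r = 0.19. By the t distribution it needs about (0.55 / 0.566)² = 0.945, so r = 0.24. By the normal formula, r = 0.2 requires 100 in total (power at 100 is 80.1%), r = 0.3 requires 96 (82.2%) and r = 0.5 requires 78 (88.8%).
- *If 0.55 is scaled to the SD of change*, the change score has variance 2σ²(1 − r) and ANCOVA has σ²(1 − r²), a ratio of (1 + r)/2. The requirement is 100 or fewer whenever (1 + r)/2 is at most 0.964 (normal) or 0.945 (t), that is for r up to about 0.93 or 0.89.

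**The case against.** The strongest reply is that the unadjusted test is not the planned one. The Main analysis section commits to baseline-adjusted ANCOVA. A correlation of about 0.2 to 0.25 is enough on the outcome-SD scale, and almost any correlation on the change-SD scale, for 100 completers to reach 80%. Even without adjustment the gap at 100 is 1.5 to 2.3 percentage points. The plan works in round numbers (400, 120, 100) for a Phase II trial with feasibility among its aims. A condensed article may also leave the test and its inputs to a fuller document.

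Most of this stands, and it limits the point in three ways.

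- A reader might infer that the trial will not have 80% power even if all 100 respond. The documents do not support that: it is true of an unadjusted two-sided test, and the planned analysis is adjusted.
- A reader might infer that, with no correlation given, 100 cannot have come from an ANCOVA calculation. That does not follow either, since an unstated input may still have been used.
- The further loss at 96 completers comes from the retention arithmetic, which is a separate slip. It should not be used to enlarge the gap at 100.

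What the reply does not remove is that the article prints a specific result beside specific inputs, and the result does not follow from them on the conventional reading. Nor does the sentence state any basis on which it would.

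**Conclusion.** The sentence is wrong as written, by a small amount and in the favourable direction. On a two-sided, 1:1, unadjusted comparison, 80% power for 0.55 needs 104 to 106 completers. At 100, power is about 78% and the effect detectable with 80% power is 0.56 to 0.57. At the 96 implied by the stated retention, power is 76 to 77% and the detectable effect 0.57 to 0.58.

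The conclusion rests on assumed sidedness and allocation ratio. It concerns the stated calculation and does not show that the planned ANCOVA lacks power, which depends on a correlation and an SD definition that the article does not give. Severity is minor: no decision on recruitment, allocation or analysis turns on it.

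**What to change.** Keep the recruitment target of 120 and restate the sentence with one consistent completer number, in one of two ways.

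- **Unadjusted power.** For example: before baseline adjustment, 100 completers give about 78% power for an effect size of 0.55, or 80% for about 0.57. If 96 is the intended number, the figures are about 76% and 0.58. The words about adjustment matter, because without them the sentence could understate the planned analysis.
- **ANCOVA power.** State the SD that defines 0.55 and the assumed baseline/follow-up correlation, and recompute the figure on that basis. This matches the planned analysis better.

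In either case, say that the test is two-sided, if it is. The cost is one sentence and, in the first form, a slightly less favourable stated power. No extra patients are needed.
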